**Figure 1 figure1:**
[figure not shown]
Study timeline. Staggered implementation of the context-adapted CISSS-CA ACE intervention across four hospitals and parallel mixed-methods process evaluation. ACE: Acute Care for Elders; CISSS-CA: Centre intégré de santé et de services sociaux de Chaudière-Appalaches (Chaudière-Appalaches Integrated Health and Social Services Centre).

**Figure 2 figure2:**
[figure not shown]
LEARNING WISDOM study design, data collection, indicators, and recruitment process. CLSC: Centres locaux de services communautaires (Local Community Services Centers); ED: emergency department; NHS SM: National Health Service Sustainability Model.

**Table 1 table1:** Primary and secondary study outcomes.

Outcomes			Data source
	
**Primary outcome**			
		Composite endpoint at each month (30-day hospital readmission and ED^a^ visit rate)	Administrative databases (Med-GPS, RAMQ^b^ billing database, and MedECHO^c^)
**Secondary outcomes**			
	**Hospital level**		
		Hospital and ED length of stay	Administrative database (Med-GPS, RAMQ billing database, and MedECHO)
		Hospital and ED admission rate	Administrative database (Med-GPS, RAMQ billing database, and MedECHO)
		Alternate level of care occupation rate	Administrative database (Med-GPS, RAMQ billing database, and MedECHO)
		Rate of patients returning to prehospital living situation	Administrative database (Med-GPS, RAMQ billing database, and MedECHO)
		Proportion of patients with family physician appointment in the 21 days after ED discharge	RAMQ billing database
	**Patient/caregiver level**		
		Quality of care transitions	Care Transition Measure (CTM-3) (48-hour postdischarge phone questionnaire)
		Functional autonomy	Chart audit to identify the PRISMA-7^d^ score and Iso-SMAF^e^ profile (case-mix classification profile according to patients’ functional autonomy characteristics as determined by the SMAF)
		Anxiety	Geriatric Anxiety Inventory-Short Form (phone questionnaire)
		Living situation at 30 days after ED discharge	Chart audit
		Burden of care	Zarit Brief Burden Interview with two additional open questions (phone questionnaire)

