#### Phase ID (Implementation, 9 Months)

In the 9 months following training and local adaptation, we will implement the context-adapted CISSS-CA ACE program with the support of WikiTrauma and local implementation teams who will have the responsibility to roll out the different elements of our intervention within their respective hospitals. Our context-adapted CISSS-CA ACE program will include a series of systematic predischarge, postdischarge, and across transition period interventions for eligible patients as follows: (1) screening of patients in need of multidimensional evaluation of their loss of autonomy (with the *Programme de Recherche sur l’Intégration des Services de Maintien de l’Autonomie 7* [PRISMA-7] tool) [76]; (2) a geriatric emergency management (GEM) nurse; (3) geriatric training [77]; (4) communication tools for transmitting information to nursing homes and other community-based stakeholders in the health system; (5) a fall prevention program; (6) systematic medication reconciliation; (7) elder-friendly ED environment adaptation; (8) access to clinician- and patient-centered Wiki-based KT tools [78,79] (eg, standing orders for geriatric patients admitted to the ED, geriatric analgesia prescription order set, and patient communication tools and decision aids); and (9) access to a community-based telemonitoring service. This service, which is offered by *Télé-Surveillance Santé - Chaudière-Appalaches* (TSS-CA) [80], will be offered for free to all eligible patients (ie, patients aged over 65 years who have at least seven ED visits in last 12 months, where over half of these visits are triaged to the ED observation unit and where two visits are not followed by hospitalization) transitioning from the hospital or ED to their home. This service currently offers remote monitoring of patients; nurses available 24 hours a day, 7 days a week, 365 days a year; and monthly phone check-ups. It also includes a customized emergency response intervention when patients are in need and connects patients with a network of community-based volunteer caregivers who are notified to visit patients when in need or simply to conduct a routine check-up.

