#### Study Comparison

Results from the centers will be compared with their own results in the preintervention period using data collected for the ITS study.

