#### Patient- and Caregiver-Level Sociodemographics and Outcomes

Patient and caregiver baseline sociodemographic data will include age, sex, race, language, education level, family income, prehospital living situation (eg, home, intermediate nursing homes, etc), geography of residence (rural vs urban: as defined by Statistics Canada for Rural and Small Town [81,82]), and reason for hospital admission or consultation in the ED. Patient and caregiver outcomes are presented in Table 1. The living situation will be noted in the medical file when available at 30 days after discharge. Other measures that will be collected after discharge include the Care Transitions Measure-3 (CTM-3) [17,83], the Geriatric Anxiety Inventory-Short Form (GAI-SF) [84,85], and the Zarit Burden Interview (ZBI) [86]. The CTM-3 is a three-item questionnaire that measures the perceived quality of care transition on a 0-4 scale (0, fully disagree; 4, fully agree). The French version of the tool will be used [87]. The GAI-SF measures anxiety among seniors. The short version comprises five questions. The French-Canadian version of the tool has good psychometric properties [88]. The ZBI measures the burden of caregivers. The brief French version (12 questions) of the scale has good psychometric properties and is comparable to the original version [89,90].

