#### Sample Size and Statistical Analysis

We will use segmented regression statistics to measure the changes in the level and slope in the postintervention period compared with the preintervention period in each center for each of our primary and secondary outcomes [92]. Thus, we will present a regression model with different intercept and slope coefficients for the pre- and postintervention time periods for each center. We will compare the changes in a composite primary outcome (total 30-day hospital readmission and ED visit rate) at our four intervention centers. We will use a Durbin-Watson test to verify the presence of autocorrelation and use an autoregressive error model to correct for this serial correlation. For an ITS, 10 measurement points before and 10 points after an intervention provide 80% power to detect a change in the level of 5 standard deviations (of the predata) only if the autocorrelation is greater than 0.4 (ie, extent to which data collected close together in time are correlated with each other) [93].

We have calculated the sample size for our patient cohort, which will be based on the smallest clinically significant difference (ie, 11%) that the CTM-3 can capture on a maximum score of 100. To detect a difference of 11% with a type I error of 5% and a type II error of 20%, 38 patients per month are needed to calculate a monthly CTM-3 estimate, based on a previous study in which CTM-3 was measured in 21 patients at Hôtel-Dieu Hospital in Lévis and showed an average of 75% and a standard deviation of 23%. Considering a call rejection rate of 70%, the number of people to be contacted in total will be 127 patients per month for each ED. We will therefore contact 5 patients per day in each of the four participating centers to obtain our targeted sample size of 38 patients at the end of the month. To ensure the creation of a random and representative sample of our population of elderly patients being discharged from the ED, a randomization table based on all patients discharged in the previous 24 hours from the ED will be provided every day to select which patients to call.

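### Functional autonomy is read partly from charted PRISMA-7 scores, and PRISMA-7 screening is itself part of the program, so a pre/post change is confounded with who gets screened

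*Protocol article*

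**What the plan says.** All references are to the protocol article.

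- **Outcome.** Table 1, patient/caregiver level, gives the source for functional autonomy as "Chart audit to identify the PRISMA-7" score and the Iso-SMAF profile. The latter is glossed as a "case-mix classification profile according to patients’ functional autonomy characteristics as determined by the SMAF". No time point is attached to this outcome.
- **Intervention.** Phase ID (Implementation, 9 Months) describes the program as "a series of systematic predischarge, postdischarge, and across transition period interventions for eligible patients". Its first listed component is "screening of patients in need of multidimensional evaluation of their loss of autonomy", carried out with the PRISMA-7. Neither the SMAF nor the Iso-SMAF profile appears among the nine components.
- **Comparison.** Under Study Comparison, "Results from the centers will be compared with their own results in the preintervention period".
- **Analysis.** Sample Size and Statistical Analysis applies segmented regression for level and slope "in each center for each of our primary and secondary outcomes".
- **Sampling.** The same section selects patients to call from "a randomization table based on all patients discharged in the previous 24 hours from the ED".
- **Other patient and caregiver measures.** The CTM-3, the anxiety inventory and the Zarit interview are asked by telephone by the research team. No functional scale is listed with them.

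**The concern.** PRISMA-7 is the one outcome instrument in Table 1 that is also named as a component of the program. Once screening is systematic, the set of patients with a charted score can change because the program is working as intended. Segmented regression attributes a shift at or after the interruption to the intervention. It has no term that separates a change in patients' function from a change in which patients were scored.

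At stake is the reading of one named secondary outcome. If clinicians had earlier scored mainly patients who looked frail, widening the screen would lower the average level of disability on record and look like a benefit. The opposite pattern of charting would look like harm or would hide a real benefit.

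**Working it through.** The plan gives no power or effect figure for this outcome, so there is nothing to reproduce. The check has two parts.

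**1. Can the design separate the two explanations?**

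- Random selection of ED discharges makes the people called representative. It does not put a score in the chart of someone whom clinicians never screened.
- Limitations names the biases that an interrupted time series can examine: underlying trend, seasonality, intervention duration, random variation and serial correlation. A change in ascertainment that coincides with the intervention is not among them.
- The telephone measures do not share the problem, because the research team asks them in both periods. PRISMA-7 comes from the chart, and the article mentions no administration of it by the research team.

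**2. How large could the artefact be?**

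Inputs, all assumed because the article gives no charting coverage:

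- true PRISMA-7-positive (frail) share p of 50% or 30%, the same before and after;
- before: coverage cn = 20% in non-frail patients and cf = r × 20% in frail patients, with r from 1 to 3;
- after: coverage of 90% in everyone.

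Observed positive share among charted patients = p·cf / [p·cf + (1 − p)·cn]. Dividing through by cn gives p·r / [p·r + (1 − p)]. Only the selectivity ratio r matters, not the coverage level itself.

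Example with p = 50%, r = 2: before, 0.5 × 0.4 / (0.5 × 0.4 + 0.5 × 0.2) = 0.20 / 0.30 = 66.7%; after, 50.0%.

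| True share | r before | Observed before | Observed after | Spurious change (points) |
|---|---|---|---|---|
| 50% | 1 | 50.0% | 50.0% | 0 |
| 50% | 1.5 | 60.0% | 50.0% | −10.0 |
| 50% | 2 | 66.7% | 50.0% | −16.7 |
| 50% | 3 | 75.0% | 50.0% | −25.0 |
| 30% | 1 | 30.0% | 30.0% | 0 |
| 30% | 1.5 | 39.1% | 30.0% | −9.1 |
| 30% | 2 | 46.2% | 30.0% | −16.2 |
| 30% | 3 | 56.3% | 30.0% | −26.3 |

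Further cases from the same formula:

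- **Opposite sign.** If charting was unselective before and selective after, the columns swap and the changes become positive, for example +16.7 points at p = 50%, r = 2.
- **True change, unselective charting.** A fall from 50% to 40% shows as 50.0% to 40.0%, even though coverage rises from 20% to 90%.
- **True change, constant r = 2.** The same fall shows as 66.7% to 0.16 / (0.16 + 0.12) = 57.1%, still a fall, of 9.5 points.
- **True change hidden.** A worsening from 40% to 50%, with r = 2 before and r = 1 after, shows as 57.1% to 50.0%. A 10-point deterioration reads as a 7.1-point improvement.

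**The case against.** The strongest reply is that the article does not describe preintervention charting, so a clean off/on switch of the instrument cannot be assumed. That stands. The abstract says that an adapted ACE program was implemented at one hospital in 2016, and the Introduction says that the adaptation had to fit the provincial senior-friendly hospital practices. Neither shows that PRISMA-7 was already charted, but both leave room for it, and coverage may differ by site. Phase ID is also a 9-month rollout and not a single date.

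A reader might go further and infer that any pre/post change merely reflects who was screened. The documents do not support that. The observed change mixes ascertainment with function, and the table shows zero bias when earlier charting was unrelated to frailty.

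A reader might also infer that the whole outcome fails. Iso-SMAF is the other half of it and is not a listed component. It may share the problem if profiles are charted mainly after a positive screen, but the article does not say so.

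Nor can one say that the audited score precedes the care transition, since no time point is given. The audit window and the handling of uncharted scores are details that a condensed article may leave to the full protocol, and their absence is not counted here.

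What the reply does not remove is the overlap itself. The source of the outcome and the screening component are both fixed in the article, and selection for reasons that the chart may not record cannot be reliably repaired by missing-data methods.

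**Conclusion.** The concern holds as confounding of unknown size and sign. Following the plan as written can produce a level change in charted PRISMA-7 when no patient's function has changed, and can mask or reverse a true change. Under the assumed selectivity of 1.5 to 3, the spurious shift in the positive share is about 9 to 26 points; with no selectivity it is nil. These figures rest entirely on assumed coverage and show what is possible, not what happened at these sites. For Iso-SMAF the problem is possible but not established. The primary composite of readmission and ED visits comes from administrative databases and is not affected, and no sample size rests on this outcome. The point should be dealt with before the functional autonomy data are analysed.

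**What to change.** - Do not interpret a segmented-regression change in charted PRISMA-7 as a program effect. Report the scores as case-mix description.
- Add to the clinical-level process outcomes in Table 1 the proportion of audited charts with a PRISMA-7 score, and the proportion with an Iso-SMAF profile, by month and site. The first also serves as a measure of fidelity to the screening component.
- Keep Iso-SMAF as an effect outcome only if its charting coverage is stable across the interruption.
- If function is to remain an effect outcome beyond that, functional items could be added to the existing telephone interview. Compare only the months in which they were asked. Data collection began in January 2019 and 1635 patients were enrolled by January 2020, so months already collected cannot be recovered.

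**Cost.** The first two changes use the chart audit already planned and need a revision of Table 1 and of the analysis wording. The price is one fewer effectiveness outcome. The telephone option adds items to a call already made and may leave some sites with few or no preintervention months.

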	**Clinical-level process**		
		Proportion of patients seen by a GEM^f^ nurse	Chart audit
		Proportion of patients/caregivers/family physicians receiving discharge summary in the 21 days following ED discharge	Postdischarge phone questionnaire and 21-day family physician follow-up phone call
		Proportion of medication patients with a reconciled medication list	Chart audit
		Proportion of eligible patients using telemonitoring services	TSS-CA^g^ telemonitoring service database

^a^ED: emergency department.

^b^RAMQ: Régie de l’assurance maladie du Québec.

^c^MedECHO: maintenance et exploitation des données pour l'étude de la clientèle hospitalière.

^d^PRISMA-7: Program of Research to Integrate the Services for the Maintenance of Autonomy.

^e^SMAF: Système de mesure de l'autonomie fonctionnelle (Functional Autonomy Measuring System).

^f^GEM: geriatric emergency management.

^g^TSS-CA: Télé-Surveillance Santé - Chaudière-Appalaches.

### Part I: Interrupted Time Series

#### Study Context

The four participating hospitals (Hôtel-Dieu de Lévis, St-Georges, Montmagny, and Thetford Mines) are part of the CISSS-CA, a new integrated health organization under the leadership of a single CEO and created in 2015 by a legislative health reform in the province of Quebec, Canada (Act to Modify the Organization and Governance of the Health and Social Services Network) [72]. The CISSS-CA has 318 health facilities within its large mixed rural and urban territory, including the four acute care hospitals in this study. Although this new supraregional organization now has the administrative infrastructure to offer integrated care, it still lacks the knowledge management infrastructure to mobilize knowledge within its organization that has 10,000 employees serving a population of more than 415,000 spread across a large territory (15,079 km^2^) [73].

#### Study Participants

##### Clinicians and Decision Makers

All hospital- and community-based clinicians and decision makers involved in care transitions will be eligible to participate. Hospital-based clinicians and decision-makers are CISSS-CA employees or independent professionals working at the participating hospitals (eg, managers, physicians, nurses, pharmacists, social workers, occupational therapists, and physiotherapists). Community-based clinicians and decision makers are CISSS-CA employees or independent professionals working outside of the hospital in a community setting (ie, home-care professionals).

##### Patients

Eligible patients will be (1) aged ≥65 years; (2) discharged from the ED; (3) able to understand and read French; and (4) able to provide informed consent.

##### Caregivers

Eligible caregivers will be identified by the patients themselves and approached only after patient consent is obtained. Caregivers will be (1) able to understand and read French and (2) able to provide informed consent.

#### Study Intervention

Our intervention is the delivery of a context-adapted CISSS-CA ACE program using a KT strategy based on our Wiki-suite. This intervention will be deployed in sequential phases.

#### Phase IA (Local Study Set-Up, 3 Months)

An executive committee will oversee the entire study (Figure 1). This committee, which will be led by the first author (PA) and Director of Nursing, will meet every month during this 4-year study. The other members include a community-based geriatric nurse specialist, a home care coordinator, the ED director, the ED head nurse, a geriatrician, a database and measurement specialist, an information technology analyst, our research coordinator, and a patient representative. A local implementation team for each participating hospital, including an ED physician, a hospitalist, a family physician, a home care nurse, an inpatient unit manager, a research assistant, and a local patient or caregiver, will also meet every month at each participating hospital starting 9 months before the active implementation of the ACE program (Phase ID). This team will include locally identified champions to lead the local implementation. Regular meetings will also be organized with local hospital and community-based clinicians and decision makers to gather relevant feedback.

#### Phase IB (Wiki101 and ACE Training, 3 Months)

All local team members and eligible health professionals or decision makers will complete the Wiki101 web-based training to learn how to navigate and edit knowledge tools in WikiTrauma. After completing Wiki101, our executive committee in collaboration with ACE experts will then offer tailored support to each local team and the local champions to implement the ACE program. The training and support aim to inform and empower the local teams by providing information on the various ACE program interventions to implement locally, the rationale for each program intervention, and the sharing of existing knowledge tools and expertise developed in each center.

#### Phase IC (Local Adaptation of Knowledge Tools, 3 Months)

The context-adapted knowledge tools created at each site will be kept in WikiTrauma [74,75]. A local working group will be created in each center. All clinicians and decision makers will be encouraged to copy, edit, and update knowledge tools within WikiTrauma to create their own context-adapted tools. Our Wiki will track all changes automatically, and we will use Google Analytics to track the use of the tools. Any changes will be reviewed during our executive committee meetings and integrated after review to ensure reliability. Partners at Mount Sinai, CFHI, and *Institut national d’excellence en santé et services sociaux* (INESSS) will also have access to these web-based tools to provide expert oversight of our tool adaptation process. For any newly developed patient-centered knowledge tools (eg, self-care management guides), we will solicit in-depth feedback from a patient representative, who will lead a subcommittee of caregiver and patient representatives from the participating sites.

#### Phase ID (Implementation, 9 Months)

In the 9 months following training and local adaptation, we will implement the context-adapted CISSS-CA ACE program with the support of WikiTrauma and local implementation teams who will have the responsibility to roll out the different elements of our intervention within their respective hospitals. Our context-adapted CISSS-CA ACE program will include a series of systematic predischarge, postdischarge, and across transition period interventions for eligible patients as follows: (1) screening of patients in need of multidimensional evaluation of their loss of autonomy (with the *Programme de Recherche sur l’Intégration des Services de Maintien de l’Autonomie 7* [PRISMA-7] tool) [76]; (2) a geriatric emergency management (GEM) nurse; (3) geriatric training [77]; (4) communication tools for transmitting information to nursing homes and other community-based stakeholders in the health system; (5) a fall prevention program; (6) systematic medication reconciliation; (7) elder-friendly ED environment adaptation; (8) access to clinician- and patient-centered Wiki-based KT tools [78,79] (eg, standing orders for geriatric patients admitted to the ED, geriatric analgesia prescription order set, and patient communication tools and decision aids); and (9) access to a community-based telemonitoring service. This service, which is offered by *Télé-Surveillance Santé - Chaudière-Appalaches* (TSS-CA) [80], will be offered for free to all eligible patients (ie, patients aged over 65 years who have at least seven ED visits in last 12 months, where over half of these visits are triaged to the ED observation unit and where two visits are not followed by hospitalization) transitioning from the hospital or ED to their home. This service currently offers remote monitoring of patients; nurses available 24 hours a day, 7 days a week, 365 days a year; and monthly phone check-ups. It also includes a customized emergency response intervention when patients are in need and connects patients with a network of community-based volunteer caregivers who are notified to visit patients when in need or simply to conduct a routine check-up.

In parallel with these interventions, we will also offer audit and feedback for health professionals and decision-makers in order to support organizational learning that will allow for real-time adjustment of interventions that are implemented. Feedback will take the form of monthly newsletters for the CISSS-CA covering patient-, clinician-, and hospital-level quality indicators. Moreover, our research team will be embedded within the CISSS-CA elder-friendly hospital committee, which plays an active role in supporting quality improvement initiatives and program implementation. This will ensure that results generated by our research team will benefit our population and ensure timely integrated knowledge translation.

